## Abstract

**Introduction:**

In 2013, a single-centre study reported the safe use of esmolol in patients with septic shock and tachycardia who required vasopressor therapy for more than 24 hours. Although not powered to detect a change in mortality, marked improvements were seen in survival (adjusted HR, 0.39; 95% CI, 0.26 to 0.59; p<0.001). Beta blockers are one of the most studied groups of drugs but their effect in septic shock is poorly understood; proposed mechanisms include not only the modulation of cardiac function but also immunomodulation.

**Methods and analysis:**

STRESS-L is a randomised, open-label, non-blinded clinical trial which is enrolling a total of 340 patients with septic shock as defined by Sepsis-3 consensus definition and a tachycardia (heart rate ≥95 beats per minute (bpm)) after vasopressor treatment of at least 24 hours. Standard randomisation (1:1 ratio) allocates patients to receive usual care (according to international standards) versus usual care and a continuous landiolol infusion to reduce the heart rate between 80 and 94 bpm. The primary endpoint is the mean Sequential Organ Failure Assessment score over 14 days from entry into the trial and while in intensive care unit. Results will inform current clinical practice guidelines.

**Ethics and dissemination:**

This trial has clinical trial authorisation from the UK competent authority, the Medicines and Healthcare products Regulatory Agency, and has been approved by the East of England-Essex Research Ethics Committee (reference: 17/EE/0368).

The results of the trial will be reported first to trial collaborators. The main report will be drafted by the trial coordinating team, and the final version will be agreed by the Trial Steering Committee before submission for publication, on behalf of the collaboration.

**Registration:**

The trial is funded by the National Institute for Health Research Efficacy and Mechanism Evaluation (EME) (Project Number: EME-14/150/85) and registered ISRCTN12600919 and EudraCT: 2017-001785-14.

Strengths and limitations of this studySTRESS-L is a randomised study comparing the use of the ultra-short acting beta blocking agent, landiolol, with standard care in patients with septic shock, persistent tachycardia treated with high-dose norepinephrine.STRESS-L will study 340 patients, which we believe will be the largest study of its type.There is little known about the effects of beta blockade and the mechanisms induced by beta-1 receptor antagonist in this population.Its limitation is that the study is not double blind since the dosing of the investigational medicinal product (landiolol) is variable according to a physiological endpoint (target heart rate of 80–94 beats per minute), a placebo would be ineffective and the intervention impossible to blind.

## Introduction

A randomised single-centre study of 154 patients from Rome^1^ reported the use of beta-adrenergic blockade using the short-acting agent esmolol in patients with septic shock and tachycardia who required vasopressor therapy for more than 24 hours. The dosing endpoint was a reduction in heart rate between 80 and 94 beats per minute (bpm). Though this study was not powered to detect a change in mortality, marked improvements were seen in survival (adjusted HR, 0.39; 95% CI, 0.26 to 0.59; p<0.001). Improvements were also seen in the beta blocker-treated group in the duration of vasopressor treatment, and in measures of renal and cardiac function.

Autonomic dysfunction and tachycardia are associated with a poor outcome in septic shock^2^ with mortalities in excess of 70%.^3^ Bradycardia is relatively protective.^4^ Currently, beta agonists are recommended as part of resuscitation and restoration of cardiac output and blood pressure in septic shock^5^ despite an early study examining the use of dobutamine to increase cardiac index and systemic oxygen delivery being stopped prematurely because of an increase in the intervention cohort.^6^ Beta blockade represents a paradigm shift in management of patients with septic shock and arises from observations of harm induced by excessive sympathetic activation and benefit from beta-adrenergic blockade. Limited data from animal models^7–12^ and patients^1 13 14^ suggest improved cardiovascular and immune function by their use. Excess beta-adrenergic activation may be both endogenous (related to the severity and duration of the underlying infection) and exogenous due to the catecholamine therapy which has until now been the mainstay of management of hypotension caused by septic shock.^5^ A combination of beta-2 agonist with beta-1 blockade improves sepsis-induced immune, cardiovascular and coagulation dysfunction in established sepsis (reviewed in^15^).

Landiolol (Rapibloc, AOP Orphan Pharmaceuticals, Vienna, Austria) is an ultra-short-acting beta blocker that has a half-life of 2.3–4 min^16^ and is approximately eight times more selective for the beta-1 receptor than esmolol.^17^ Landiolol is metabolised by plasma pseudocholinesterase and liver carboxylesterse to inactive metabolites and its metabolism is unaffected by liver impairment.^18^ A few preclinical studies have examined landiolol in sepsis. It decreased circulating levels of the cytokines, tumour necrosis factor (TNF)-alpha, interleukin (IL)-6, and high mobility group box-1 and reduced histological lung damage in a rat endotoxin model.^11^ Landiolol was also cardioprotective in rats with septic shock by normalising the expression of cardiac vasoactive peptide endothelin-1.^19^ Landiolol has been used safely and successfully in a patient with septic shock with atrial fibrillation^20^ and in sepsis-induced tachycardia.^21^ A recent trial of 151 patients from 54 centres in Japan^22^ demonstrated that landiolol could be safely administered to patients with septic shock.

Landiolol rather than esmolol was selected for this clinical trial because of its superior beta-1 specificity and the expectation that stopping the landiolol infusion would allow a rapid return to the baseline haemodynamic state if investigators deemed the intervention harmful. We will also report data of safety of landiolol infusion as part of the study.

## Study objectives

### Primary objective

The primary objective of this trial is to assess the efficacy, safety and mechanisms of landiolol (beta blockade) in patients with septic shock and tachycardia requiring prolonged (>24-hour continuous treatment) support with high-dose vasopressor agents.

### Secondary objectives

The secondary objectives of the trial are:

To determine whether infusion of the rapid-acting, ultra-short-lived and highly specific beta-adrenergic antagonist landiolol improves mortality and length of hospital stay compared with current best clinical practice, in patients who have septic shock.To investigate the pathways that are altered by beta blockade in septic shock by examining the effects of landiolol on blood markers of inflammation, metabolism and cardiomyocyte damage.

## Methods and analysis

This manuscript has been written in concordance with the Standard Protocol Items: Recommendations for Interventional Trials guidelines.^23^

### Trial design

This is a multicentre, randomised, controlled open label phase IIb trial comparing usual treatment with usual treatment plus landiolol infusion in a total of 340 patients. The trial is conducted and managed by Warwick Clinical Trials Unit and sponsored by the University Hospitals of Birmingham (UHB) National Health Service Foundation Trust. It is coordinated by a Trial Management Group and independent oversight is provided by the Trial Steering Committee and a Data Monitoring Committee.

The trial has been designed and will be reported in line with the CONSORT (Consolidated Standards of Reporting Trials) statement^24^ and the conduct has been planned in full conformance with the principles of the Declaration of Helsinki and Good Clinical Practice.

### Study setting

The study recruitment commenced in May 2018. The main trial is taking place in over 35 UK adult intensive care units (ICUs). Participating ICUs will have a typical case mix for UK critical care, a track record of recruitment to clinical trials, suitable support for screening and data collection, and the means to store blood samples for transfer to the central analysis unit. They should also be willing to manage atrial fibrillation with correction of potassium, magnesium and amiodarone in the usual care group as the use of beta blockers in these patients would risk making the trial results uninterpretable.

### Inclusion criteria

Patients are eligible to be included in the trial if they meet the following criteria:

Aged 18 years or above.Being treated in a critical care unit.Septic shock according to internationally accepted definitions.*Heart rate ≥95 bpm (at the time of randomisation).Receiving vasopressor support to maintain a target blood pressure for ≥24 hours.Are being treated with norepinephrine at a rate ≥0.1 µg/kg/min.

*Sepsis-3 definitions^25^:

Confirmed or suspected infection requiring antibiotic therapy.New organ dysfunction, as evidenced by an increase in Sequential Organ Failure Assessment (SOFA) score ≥2.A blood lactate >2 mmol/L at any point during shock resuscitation.Vasopressor therapy to maintain mean arterial pressure (MAP) ≥65 mm Hg.

In particular, the presence of a blood lactate >2 mmol/L is only necessary for the diagnosis of septic shock and is NOT necessary for randomisation 24 hours later.

### Exclusion criteria

The participant may not enter the trial if any of the following applies:

Tachycardia as a result of pain, discomfort from medical devices (including endotracheal tubes), during interventions or other patient distress.Any form of vasodilatory shock that is not caused by sepsis.Norepinephrine infusion <0.1 µg/kg/min.>72 hours after start of vasopressor therapy.<12 hours since norepinephrine to treat a medical condition other than septic shock stopped.Having pre-existing severe cardiac dysfunction (New York Heart Association grade 4 or more).Having pre-existing severe pulmonary hypertension (mean pulmonary artery pressures >55 mm Hg).Acute severe bronchospasm (due to asthma or chronic obstructive pulmonary disease).Untreated second or third degree heart block.Untreated phaeochromocytoma.Prinzmetal’s angina.A history of ischaemic stroke or transient ischaemic attack or untreated severe carotid stenosis.Advanced liver disease with Child-Pugh score of ≥B.Known sensitivity to beta blockers.Patient/legal representative unwilling to provide written informed consent.Known to be pregnant.Terminal illness other than septic shock with a life expectancy <28 days.Participants who have been administered an investigational medicinal product (IMP) for another research trial in the past 30 days.Patients in whom the clinical team feel are about to finish their norepinephrine therapy.Decision of withdrawal of care is in place or imminently anticipated.Receiving extracorporeal membrane oxygenation treatment.

Co-enrolment of study participants onto other interventional studies will be considered where there is no possible conflict with the STRESS-L trial objectives.

### Consent

Eligible patients who are deemed competent will be provided with a copy of the patient information sheet before informed consent is sought. However, due to the nature of the underlying condition and its treatment, many patients will be unable to give informed consent. The vulnerability of this patient group is fully appreciated and every effort must be undertaken to protect their safety and well-being. To ensure this, consenting will be obtained in accordance with the Medicines for Human Use Regulations and the Health Research Authority ethics guide on medical research involving adults who cannot consent (http://www.hra.nhs.uk/resources/before-you-apply/consent-and-participation/adults-unable-to-consent-for-themselves/).

### Intervention

Participants will be randomised to either usual care (control group) or usual care and landiolol (intervention group).

#### Usual care

Participants randomised to this arm will receive usual care for septic shock, namely:

Timely treatment of the source of sepsis (eg, drainage of infected fluid collections).Prompt and appropriate empirical antibiotic treatment, and modification, if needed, on the basis of culture results.Appropriate fluid resuscitation to correct hypovolaemia.The use of vasopressors to achieve a target MAP (suggested target 65–70 mm Hg).

Adequate fluid resuscitation will be achieved using repeated fluid challenges to a guided target; the use of a cardiac output monitor is not mandated. The usual care group will not receive any beta blockade for the duration of their ICU stay—if the treating clinician deems beta blockade necessary, this will be captured on the Case Report Form (CRF) and reported as a protocol deviation. All other general ICU management will be based on the latest guidance from the surviving sepsis campaign^5^ and the UK national critical care guidelines (eg, ventilator and central line care bundles).

#### Usual care and landiolol

An intravenous infusion of landiolol will be started at 1.0 µg/kg/min and will progressively increase every 15 min at increments of 1.0 µg/kg/min, to reach the target heart rate of 80–94 bpm usually within 6 hours. Landiolol will be administered peripherally or centrally but must be on a dedicated line. Landiolol has an elimination half-life of 2.3–4 min^17^ and so a loading dose is unnecessary. The landiolol infusion will be continued until the pulse rate is persistently below 95 bpm.

While a patient is receiving vasopressor agents (norepinephrine, vasopressin), the landiolol infusion will be adjusted accordingly to maintain the target heart rate of 80–94 bpm as per the landiolol infusion protocol (figure 1: STRESS-L Study drug infusion protocol). Once the patient is consistently within the target heart rate of 80–94 bpm, the landiolol infusion will be continued and not be adjusted. The landiolol should be weaned and, if necessary, stopped while the heart rate is below 80 bpm. Once all vasopressor agents have been discontinued:

If vasopressors have been discontinued for less than 12 hours, the landiolol infusion will continue according to figure 1.If vasopressors have been discontinued for more than 12 hours, the landiolol should be actively weaned (this is the end of norepinephrine treatment (EONT) timepoint) and according to figure 2: Timing and weaning of the study drug.

This trial allows for up to 14 days of landiolol treatment per participant.

**Figure 1 F1:**
[figure not shown]
STRESS-L Study drug infusion protocol. bpm, beats per minute; HR, heart rate.

**Figure 2 F2:**
[figure not shown]
STRESS-L protocol for weaning and stopping of study drug. bpm, beats per minute; HR, heart rate.

## Outcome measures

### Primary outcome

The primary outcome will be the mean SOFA score over the first 14 days from entry into the trial and while in ICU. Measurement of the SOFA score will cease if the patient withdraws from the trial, dies or is discharged from the ICU. It is assumed that delayed discharges will be evenly distributed between each group.

### Secondary outcomes

Mortality at day 28 and day 90.Length of ICU and hospital stay.Reduction in dose and duration of vasopressor treatment (total daily administered doses).

### Mechanistic outcomes

Serial blood samples will be collected from patients and assays will include markers of myocardial dysfunction and inflammation.

Measurement of total catecholamine. It is unknown whether beta blockade acts through altering the effects of extraneous catecholamines administered as treatment of septic shock or by modulating those produced by the patient. Serum catecholamines will be analysed in the context of the dose of inotropes being administered.Markers of myocardial dysfunction. Serum B-type natriuretic peptide has been demonstrated to be a reliable biomarker of myocardial injury, ischaemia and dysfunction in patients with septic shock and also as a prognostic marker for a poor outcome.^26 27^ Serial measurements of troponin-T will be made.Measurement of serum free fatty acids and markers of fatty acid metabolism.Biomarkers of systemic inflammation. This will be measured using a multiplex inflammatory biomarker assay depending on the available technology at the time of analysis. A selection of cytokines will be analysed, all or some of which will include IL-1 beta, IL-2, IL-4, IL-5, IL-6, IL-8, IL-10, IL-12, TNF-alpha, TNF-beta and interferon-gamma. This focused array will allow an assessment of the pro/anti-inflammatory balance over time in patients with septic shock and allow more detailed study of the other potential mechanisms of action of landiolol. Cortisol assays will measure the influence of beta blockade on the adrenal cortex.In addition, samples will be stored for subsequent analysis (eg, genetics/proteomics/metabolomics) in order to investigate early cellular responses during the resolution of sepsis.

### Safety outcomes

The episodes of bradycardia (heart rate <50 bpm), bradycardia with haemodynamic compromise requiring intervention, significant hypotension requiring intervention (not including temporarily stopping the infusion), heart block, arrhythmia and arrhythmia with haemodynamic compromise requiring intervention will be reported.

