#### Baseline visit 24 hours prior and up to randomisation

Table 1 summarises the schedule of events for the trial. The patient’s medical history, physical examination, basic demographic data and steroid use will be recorded. The participant will be randomised, and if allocated to the landiolol arm, IMP will be dispensed and the infusion started. As there is no checking and preparation of drug in the usual care arm, the landiolol infusion should be started within 1 hour of randomisation. The elements of the SOFA score will be recorded along with routine clinical data (cardiovascular, respiratory and renal physiological variables as well as haematological, biochemical and microbiological sample test results). The rates of norepinephrine infusion will be recorded hourly. The site and types of pathogens isolated following admission should be recorded on the electronic CRF (eCRF).

**Table 1 T1:** STRESS-L schedule of interventions

Procedure (time (T) in days/hours)	Screening (T0–12)	Baseline (day 0–24 hours—T0)	Day 1 (T0+24)	Day 2	Day 3	Day 4	Day 5	Day 6	Day 7	Day 8	Day 9	Day 10	Day 11	Day 12	Day 13	Day 14	EONT visit	FU visit day 28	Final visit day 90
Eligibility assessment	●																		
Informed consent		●																	
Randomisation		●																	
Demographics		●																	
Medical history		●																	
ECG		●	According to clinical need or if adverse event (AE)/serious AE (SAE)																
Pregnancy test		●																	
IMP		Dispense														End			
Blood sample		●	●	●		●		●									●		
Biobank blood sample (optional)		●	●														●		
Transport of stored serum																	Batch		
Local laboratory tests (normal clinical care):		●	●	●	●	●	●	●	●	●	●	●	●	●	●	●	●		
C reactive protein		●	●	●	●	●	●	●	●	●	●	●	●	●	●	●	●		
Glucose		●	●	●		●		●									●		
Lactate		●	●	●		●		●									●		
Worst PaO_2_/FiO_2_		●	●	●	●	●	●	●	●	●	●	●	●	●	●	●	●		
Platelets		●	●	●	●	●	●	●	●	●	●	●	●	●	●	●	●		
Creatinine		●	●	●	●	●	●	●	●	●	●	●	●	●	●	●	●		
Bilirubin		●	●	●	●	●	●	●	●	●	●	●	●	●	●	●	●		
White cell count		●	●	●	●	●	●	●	●	●	●	●	●	●	●	●	●		
Liver function tests (ALT or AST)		●	●	●		●		●									●		
Central venous blood gas (BG)/ arterial BG		●	●	●		●		●									●		
Microbiology results from local lab		●	●	●	●	●	●	●	●	●	●	●	●	●	●	●	●		
Heart rate (hourly: T0+7 days)		●	●	●	●	●	●	●	●	●	●	●	●	●	●	●	●		
Atrial fibrillation (hourly: T0+7 days)		●	●	●	●	●	●												
Blood pressure (hourly: T0+7 days)		●	●	●	●	●	●												

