## Safety, ethics and dissemination

### Adverse outcomes

All SAEs and suspected unexpected SAEs occurring from the time of randomisation to the final follow-up visit at day 90 will be recorded on the CRF and faxed or emailed to the coordinating centre within 24 hours of the research staff becoming aware of the event. In particular, bradycardia (heart rate <50 bpm) with haemodynamic compromise requiring intervention, heart block, significant hypotension requiring intervention and arrhythmia with haemodynamic compromise requiring intervention should be recorded. AE/reactions will be assessed for seriousness and reported in accordance with Medicines and Healthcare products Regulatory Agency (MHRA) guidelines.

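### Hypotension managed only by pausing landiolol is not counted, and because usual care has no infusion to pause, the exclusion can lower the landiolol count alone

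*Protocol article*

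**What the plan says.** The Safety outcomes section of the protocol article lists the events to be reported. Hypotension appears as "significant hypotension requiring intervention (not including temporarily stopping the infusion". Bradycardia and arrhythmia are each listed at two levels, any episode and episodes with haemodynamic compromise that needed treatment. Hypotension is listed at the treated level only.

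Only one arm receives the infusion: "Participants will be randomised to either usual care (control group) or usual care and landiolol (intervention group". There is no dummy infusion in the control arm, because "a placebo would be ineffective and the intervention impossible to blind". The Usual care section also bars beta blockade in the control arm and treats any use as a protocol deviation. Hypotension in either arm can be met with fluid or with vasopressors: "The use of vasopressors to achieve a target MAP (suggested target 65–70 mm Hg".

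The Introduction gives as one reason for choosing landiolol that stopping it should quickly restore the earlier haemodynamic state. The Adverse outcomes section names the same event for recording, without the bracketed exclusion: "significant hypotension requiring intervention and arrhythmia with haemodynamic compromise requiring intervention should be recorded".

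**The concern.** The bracket sets a rule about what counts as an intervention. A fall in blood pressure on landiolol that resolves once the drug is paused does not count. A similar fall in usual care has no such remedy. If it is treated, it is treated with fluid or vasopressor, and it counts. The exclusion therefore works in one arm only and in one direction only.

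A pause is also a likely first response. The drug was chosen partly because its effect wears off fast, and its stated half-life is 2.3–4 min.

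At stake is what the trial can say about hypotension when a beta blocker is given to patients who depend on vasopressors. Safety is part of the primary objective, which is "to assess the efficacy, safety and mechanisms of landiolol (beta blockade) in patients with septic shock and tachycardia". With the outcome as written, equal hypotension could be reported as fewer episodes on landiolol, and a modest true excess could be reported as no difference.

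**Working it through.** **Which infusion is meant.** Norepinephrine also runs in both arms, but stopping a vasopressor does not treat hypotension. The excluded action can sensibly mean only a pause of landiolol.

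**Which episodes are lost.** The bracket qualifies the word intervention, which gives three cases on landiolol:

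- Pause plus fluid or more vasopressor: counted, because another intervention was needed.
- Permanent discontinuation: not covered by the exclusion, which names temporary stops only.
- Temporary pause and nothing else: not counted.

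Only the third group is lost.

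**Size.** The article gives no figure for hypotension, so there is nothing to reproduce. Let s be the share of landiolol episodes managed solely by a temporary pause. The documents do not give s, and every value below is an assumption. Equal recording in both arms is also assumed, and each pause-only episode is treated as equivalent to one that would have counted in usual care. Then:

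recorded ratio (landiolol / usual care) = true ratio × (1 − s)

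| Assumed s | Recorded ratio if true ratio is 1.00 | Recorded ratio if true ratio is 1.20 | True ratio if recorded ratio is 1.00, 1/(1 − s) |
|---|---|---|---|
| 10% | 0.90 | 1.08 | 1.11 |
| 25% | 0.75 | 0.90 | 1.33 |
| 50% | 0.50 | 0.60 | 2.00 |

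A true ratio of 1.20 is recorded as 1.00 when s = 1 − 1/1.20 = 16.7%.

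**What two counts would show.** Suppose landiolol has 75 episodes that count now and 25 managed by a pause alone, against 100 in usual care. The current outcome gives 75/100 = 0.75. The combined total gives (75 + 25)/100 = 1.00. A reader would see 0.75 to 1.00 instead of 0.75 alone.

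**Whether other scheduled data recover the lost episodes.**

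- The section on day 1 to day 14 has the landiolol rate recorded hourly until day 2 and 6-hourly after that. Treatment may last 14 days, or 14 × 24 = 336 h. If hourly recording covers 48 h, the other 288 h (288/336 = 86%) have only 6-hourly readings.
- Table 1 schedules "Blood pressure (hourly: T0+7 days", at most 7 × 24 = 168 h, or half of 336 h.
- Five half-lives are 5 × 2.3 = 11.5 min to 5 × 4 = 20 min, so a dip that a pause settles can fall between hourly readings.
- None of these items records why the drug was paused. Low blood pressure is not the only reason: "The landiolol should be weaned and, if necessary, stopped while the heart rate is below 80 bpm".

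These data can support a count of pause-only episodes but cannot replace it.

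**The case against.** The strongest reply is that the rule is sound. Pausing a titrated, very short-acting drug is close to routine dose adjustment. Leaving it out keeps the outcome to hypotension serious enough to need further treatment. Counting pauses would create the opposite imbalance, because a pause is an extra response that usual care lacks, and some pause-only episodes might have gone untreated in usual care. This stands, and it is why the current outcome should be kept. It does not make the single count sufficient, since that count is only the lower of two reasonable readings.

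The reply also points to material not shown. The figures with the infusion and weaning rules are missing, and the full protocol or statistical analysis plan may collect pause reasons or tabulate pauses. That is fair, and the point does not rest on missing detail. It rests on a counting rule that the article states.

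A reader might infer more than the documents support, in four ways:

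- That every episode in which landiolol was paused is dropped. The wording does not say this; an episode that also needed fluid or vasopressor still counts.
- That the Adverse outcomes section contradicts the Safety outcomes section. It uses a shorter label for the same event in a section about event recording, which is not a firm contradiction.
- That the net bias is known to favour landiolol. The trial is open label, recording may differ between arms, and the documents do not settle the net direction.
- That counting pauses would restore the true comparison. It gives an upper reading, which may overstate hypotension on landiolol.

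Other safeguards exist. Vasopressor dose and duration is a secondary outcome, adverse events are scheduled daily in both arms, and the data monitoring committee reviews safety every 6 months. They limit the consequence but do not give the missing count.

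**Conclusion.** The point holds in a limited form. Hypotension managed solely by a temporary pause of landiolol is not counted, and this exclusion can lower only the landiolol count. The between-arm comparison can therefore understate hypotension on landiolol.

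The documents do not allow the amount to be estimated. The ratios in the table follow from assumed shares and equal recording, and they show how the reported ratio would move, not what to expect in this trial. The reading of the rule itself needs no such assumption; it follows from the wording and from the absence of an infusion in usual care.

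This is a minor improvement to safety reporting. The primary outcome and the sample size are unaffected.

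**What to change.** Keep the current hypotension outcome as a measure of severity, and make three additions:

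1. A separate line for hypotension managed solely by a temporary pause of landiolol, where the pause was made for low blood pressure. Pauses made because the heart rate fell below 80 bpm do not belong here, and neither do permanent discontinuations.
2. A combined total by randomised group. Present the current count as the lower and the combined total as the upper reading for landiolol.
3. Matching wording in the Adverse outcomes section, so that pause-only episodes are recorded.

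Optionally, compare the hourly blood pressure readings between arms, for example the proportion per patient below a mean arterial pressure of 65 mm Hg, with the patient as the unit. This is supporting evidence only, because hourly readings miss short dips, stop at 7 days and partly reflect unblinded titration.

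The cost is small: a change of wording, one table line with its total, and possibly one eCRF item for the reason for a pause. Visits and sample size do not change. There are two downsides. Reasons may be incomplete for the 109 of 340 patients (32%) already recruited when the article was submitted, although 340 − 109 = 231 were still to come. The combined total may also overstate hypotension on landiolol, so it should always be shown beside the current count.
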